#### **8.7.4.1 Humoral immunogenicity studies for Part A (Wyeth)**

Evaluation of binding antibody production against IL-12 will be performed on cryopreserved samples stored at the CSR at baseline, at the 2 weeks post-vaccination visits, and at the final study visit.

#### **8.7.4.2 Humoral immunogenicity studies for Part B (Wyeth)**

Evaluation of binding antibody production against IL-12 will be performed on cryopreserved samples stored at the CSR at baseline; 2 weeks post first, second and third vaccination visits; and at the final study visit.

Evaluation of binding and neutralizing antibody production against GM-CSF will be performed on cryopreserved samples stored at the Central Specimen Repository (CSR) at baseline and 2 weeks post-fourth and fifth vaccination visits, and at the final study visit.

Neutralizing antibodies to GM-CSF will be assessed by a TF-1 cell proliferation assay, which evaluates the neutralization of GM-CSF biological activity by detecting decreased proliferation of a GM-CSF-dependent cell line (TF-1), using samples obtained at baseline; 2 weeks post fourth and fifth vaccination visits; and at the final study visit. Evaluations will be performed only on samples with demonstrated binding antibody by ELISA.

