## 7 Study type, study population, and eligibility criteria

The study is a Phase I multicenter, randomized, placebo-controlled, double-blind trial to evaluate the safety and immunogenicity of HIV-1 *gag* DNA vaccine alone and in combination with *IL-12* DNA adjuvant as a 3 dose priming series. Due to differences in injection volumes, study participants and study staff cannot be blinded to study group assignment. The study is double-blinded regarding vaccine study product versus placebo administration. Participants in Part B will also receive 2 booster vaccinations either with the above plasmids or with HIV CTL MEP vaccine or with placebo. Participants will be recruited and screened. Those determined to be eligible, based on the inclusion and exclusion criteria (see Table 7-1 and Table 7-2), will be enrolled in the study and followed for a total period of 9 months in Part A and 15 months in Part B.

Participants will receive priming series vaccinations at Days 0, 28, and 84 (Months 0, 1 and 3). Booster vaccinations for participants in Part B will be administered at Days 168 and 273 (Months 6 and 9). All vaccinations will be administered by intramuscular injection in the deltoid using needle/syringe in the outpatient setting.

Participants will be healthy HIV-1-uninfected (seronegative) adults who comprehend the purpose of the study and have provided written informed consent.

See Table 7-1 for inclusion criteria and Table 7-2 for exclusion criteria. Final eligibility determination will depend on results of laboratory tests, medical history, physical examinations, and answers to the self-administered and/or interview questions.

See Table 12-1 for screening procedures.

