- C1: Placebo for HIV *gag* DNA Plasmid 0.75 mL IM in same deltoid at months 0, 1, and 3 (unless medically contraindicated for that deltoid).

### Group 2

- T2: HIV *gag* DNA Plasmid 1500 mcg admixed with *IL-12* DNA 100 mcg administered as 0.8 mL IM in same deltoid at months 0, 1, and 3 (unless medically contraindicated for that deltoid).
- C2: Placebo for HIV *gag* DNA Plasmid / *IL-12* DNA 0.8 mL IM in same deltoid at months 0, 1, and 3 (unless medically contraindicated for that deltoid).

### Group 3

- T3: HIV *gag* DNA Plasmid 1500 mcg admixed with *IL-12* DNA 500 mcg administered as 1 mL IM in same deltoid at months 0, 1, and 3 (unless medically contraindicated for that deltoid).
- C3: Placebo for HIV *gag* DNA Plasmid / *IL-12* DNA 1 mL IM in same deltoid at months 0, 1, and 3 (unless medically contraindicated for that deltoid).

*Group 4*

- T4: HIV *gag* DNA Plasmid 1500 mcg admixed with *IL-12* DNA 1500 mcg administered as 1.5 mL IM in same deltoid at months 0, 1, and 3 (unless medically contraindicated for that deltoid).
- C4: Placebo for HIV *gag* DNA Plasmid / *IL-12* DNA 1.5 mL IM in same deltoid at months 0, 1, and 3 (unless medically contraindicated for that deltoid).

*Group 5*

- T5: HIV *gag* DNA Plasmid 1500 mcg administered as 0.75 mL IM in same deltoid at months 0, 1, 3, 6 and 9 (unless medically contraindicated for that deltoid).
- C5: Placebo for HIV *gag* DNA Plasmid 0.75 mL IM in same deltoid at months 0, 1, 3, 6 and 9 (unless medically contraindicated for that deltoid).

*Group 6*

- T6: HIV *gag* DNA Plasmid 1500 mcg admixed with *IL-12* DNA 1500 mcg administered as 1.5 mL IM in same deltoid at months 0, 1, 3, 6 and 9 (unless medically contraindicated for that deltoid).
- C6: Placebo for HIV *gag* DNA Plasmid / *IL-12* DNA 1.5 mL IM in same deltoid at months 0, 1, 3, 6 and 9 (unless medically contraindicated for that deltoid).

*Group 7*

- T7: HIV *gag* DNA Plasmid 1500 mcg admixed with *IL-12* DNA 1500 mcg administered as 1.5 mL IM in same deltoid at months 0, 1, and 3 (unless medically contraindicated for that deltoid)
- and
- HIV CTL Peptides 1000 mcg admixed with RC529-SE 50 mcg and GM-CSF 250mcg administered as 1 mL IM in same deltoid at months 6 and 9 (unless medically contraindicated for that deltoid).
- C7: Placebo for HIV *gag* DNA Plasmid admixed with Placebo for *IL-12* DNA 1.5 mL IM in same deltoid at months 0, 1, and 3 (unless medically contraindicated for that deltoid)
- and

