| T cell subsets                 | Local          | Local          | EDTA   | 5      | —                | 5               | —        | —           | —         | 5           | —         | —           | —          | 5            | —          | 5            | 25          |       |
| Immunogenicity assays          |                |                |        |        |                  |                 |          |             |           |             |           |             |            |              |            |              |             |       |
| HLA typing                     | CSR            | Duke           | ACD    | —      | 20               | —               | —        | —           | —         | —           | —         | —           | —          | —            | —          | —            | 20          |       |
| Humoral assay                  |                |                |        |        |                  |                 |          |             |           |             |           |             |            |              |            |              |             |       |
| HIV Binding ELISA              | CSR            | Duke           | SST    | —      | 5                | —               | —        | —           | —         | —           | —         | 5           | —          | 5            | —          | 5            | 20          |       |
| Ab to GM-CSF                   | CSR            | Wyeth          | SST    | —      | 5                | —               | —        | —           | —         | —           | —         | 5           | —          | 5            | —          | 5            | 20          |       |
| Ab to IL-12                    | CSR            | Wyeth          | SST    | —      | 5                | 5               | —        | 5           | —         | 5           | —         | —           | —          | —            | —          | 5            | 25          |       |
| Cellular assays                |                |                |        |        |                  |                 |          |             |           |             |           |             |            |              |            |              |             |       |

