## Appendix D: Procedures at HVTU

| Procedure                                                    |         | Visit           |      |      |      |      |      |      |      |      |      |      |      |      |      |
|--------------------------------------------------------------|---------|-----------------|------|------|------|------|------|------|------|------|------|------|------|------|------|
|                                                              | Visit:  | 01 a | 02   | 03   | 04   | 05   | 06   | 07   | 08   | 09   | 10   | 11   | 12   | 13   | Post |
|                                                              | Day:    | Screening       | D0   | D14  | D28  | D42  | D84  | D70  | D168 | D182 | D273 | D287 | D364 | D455 |      |
|                                                              | Month:  |                 | M0   | M.5  | M1   | M1.5 | M3   | M3.5 | M6   | M6.5 | M9   | M9.5 | M12  | M15  |      |
|                                                              | Part A: |                 | VAC1 |      | VAC2 |      | VAC3 |      |      |      |      |      |      |      |      |
| Part B:                                                      |         | VAC1            |      | VAC2 |      | VAC3 |      | VAC4 |      | VAC5 |      |      |      |      |      |
| Study procedures                                             |         |                 |      |      |      |      |      |      |      |      |      |      |      |      |      |
| Signed screening consent (if used)                           |         | X               | –    | –    | –    | –    | –    | –    | –    | –    | –    | –    | –    | –    | –    |
| Assessment of understanding                                  |         | X               | –    | –    | –    | –    | –    | –    | –    | –    | –    | –    | –    | –    | –    |
| Signed protocol consent                                      |         | X               | –    | –    | –    | –    | –    | –    | –    | –    | –    | –    | –    | –    | –    |
| Medical history                                              |         | X               | –    | –    | –    | –    | –    | –    | –    | –    | –    | –    | –    | –    | –    |
| Complete physical exam                                       |         | X               | –    | –    | –    | –    | –    | –    | –    | –    | A    | –    | –    | B    | –    |

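### In Part B, no anti-IL-12 antibody result is scheduled two weeks after Group 6's fourth and fifth IL-12 DNA doses; the first post-boost result comes at Day 455

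*Protocol*

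**What the plan says.** Section 8.7.4.2 schedules Part B anti-IL-12 binding antibody on specimens "stored at the CSR at baseline; 2 weeks post first, second and third vaccination visits; and at the final study visit". The anti-IL-12 row of Appendix C agrees: 5 mL at Visits 2, 3, 5, 7 and 13, dashes at Visits 8 to 12, and a row total of 25 mL.

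Section 13.1 has Group 6 receiving *gag* DNA with *IL-12* DNA, "administered as 1.5 mL IM in same deltoid at months 0, 1, 3, 6 and 9". Section 7 puts the boosts at Days 168 and 273. Group 5 receives no IL-12 DNA, and Group 7 switches to the peptide vaccine for its boosts, so only Group 6 gets IL-12 DNA at doses 4 and 5.

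Two other schedules serve as comparators. In Part A, section 8.7.4.1 takes anti-IL-12 specimens "at baseline, at the 2 weeks post-vaccination visits, and at the final study visit". In Part B, section 8.7.4.2 takes anti-GM-CSF specimens "at baseline and 2 weeks post-fourth and fifth vaccination visits, and at the final study visit"; months 6 and 9 are when Group 7 receives GM-CSF.

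**The concern.** The Part B anti-IL-12 schedule suits a regimen whose IL-12 DNA stops after the third vaccination. That describes Group 7 but not Group 6, the group with the largest planned IL-12 DNA exposure. The two doses that separate Group 6 from Group 7 on IL-12 are the two with no scheduled two-week antibody result.

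Neither IL-12 plasmid had been given to humans (section 4.2), and the safety of IL-12 DNA with homologous boosting is part of a Part B primary objective (section 6.1). The only anti-IL-12 antibody result in the protocol is negative and follows three doses in macaques (section 3.1.2.5). The macaque study in Table 3-1 that included a fourth dose reports on anti-IL-15 antibody and gives no anti-IL-12 result. Nothing shown speaks to a fourth or fifth dose. If Group 6 mounted an antibody response to the boosts that faded before the final visit, the planned testing would not show it.

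**Working it through.** This is schedule arithmetic; no power or sample-size formula applies.

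**The protocol's own figure.** Five draws (Visits 2, 3, 5, 7, 13) × 5 mL = 25 mL, which matches the Appendix C row total and the five timepoints in section 8.7.4.2.

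**Visit days.** Visits 2, 3, 5, 7 and 9 fall on Days 0, 14, 42, 98 and 182 (Appendix C). The last four Part B visits, 10 to 13, are "D273 | D287 | D364 | D455" in Appendix D. Two discrepancies do not affect the result:

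- Appendix D prints D70 for Visit 7, which would precede the Day 84 vaccination. Day 98 from Appendices B and C fits 84 + 14.
- Appendix C prints D288 for Visit 11, where Appendix D has D287.

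**Two-week coverage of each IL-12 DNA dose in Group 6.**

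| Dose | Day given | Day two weeks later | Anti-IL-12 scheduled? |
|---|---|---|---|
| 1 | 0 | 14 | yes (Visit 3) |
| 2 | 28 | 42 | yes (Visit 5) |
| 3 | 84 | 98 | yes (Visit 7) |
| 4 | 168 | 182 | no (Visit 9) |
| 5 | 273 | 287 | no (Visit 11) |

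Two of five doses have no two-week result scheduled.

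**Intervals.**

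- No scheduled measurement: 455 − 98 = 357 days.
- Dose 4 to first post-boost result: 455 − 168 = 287 days.
- Dose 5 to first post-boost result: 455 − 273 = 182 days, about six months.

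**Planned cumulative IL-12 DNA.** Group 6: 5 × 1500 = 7500 mcg. Groups 4 and 7: 3 × 1500 = 4500 mcg. Section 8.4 leaves the Part B dose to the Part A safety review, so these totals could change; the contrast of five doses with three would not.

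**Serum in store.** Appendix C stores 15 mL of serum at each of Visits 8 to 13, including Visits 9 and 11.

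**Do the optional-testing provisions close the gap?** Section 8.7 allows stored specimens from further timepoints to be tested if responses are positive at the primary immunogenicity timepoint. The immunogenicity endpoints in section 9.3.2 are HIV-specific ELISpot and ICS, which would not flag anti-IL-12 antibody. Section 8.7.4 permits further assays of interest on cryopreserved samples but commits to none. The closing note to Appendix C names Visits 7 and 13, both already on the anti-IL-12 schedule. So these provisions allow the testing without requiring it.

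**The case against.** The case on the other side is substantial. The assay is listed as ancillary in section 8.7.4 and Table 12-2. It is not among the objectives or the endpoints of section 9.3, and the protocol does not undertake to conclude that boosted participants are free of anti-IL-12 antibody. Text and appendix agree, so nothing is contradictory. Clinical and laboratory safety follow-up continues at Visits 9 and 11. Every vaccinee planned to receive 1500 mcg (Groups 4, 6 and 7: 10 + 30 + 30 = 70) is scheduled for sampling two weeks after each of the first three doses. All of this stands, and it limits the weight of the point.

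A reader might also infer more than the documents support:

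- *That no post-boost sample exists, or that the information is lost.* Serum is stored at both two-week post-boost visits; only the assay is unassigned. A signal at Day 98 or Day 455 could be traced back through it.
- *That anti-IL-12 is never measured after boosting.* Day 455 follows both boosts and is on the schedule. A persistent response would still be tested for there, so the exposure is to a transient one.
- *That boosting is when such antibody is most likely to arise.* Nothing in the protocol shows this. Section 2.4.1 reports that anti-GM-CSF antibody faded gradually once GM-CSF stopped, which makes a transient response plausible by analogy but gives it no probability.
- *That the GM-CSF antibody tubes in Groups 5 and 6 are wasted.* These groups never receive GM-CSF and so act as concurrent unexposed controls. That has value, since section 2.4.1 reports neutralizing antibody in 0.3% of healthy plasma donors.

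**Conclusion.** The point holds as a gap in an ancillary safety-related schedule. For all 30 Group 6 vaccinees, two of five IL-12 DNA doses have no scheduled two-week anti-IL-12 result, and the first scheduled post-boost result comes 182 days after the last dose. This departs from the pattern the protocol follows for anti-IL-12 in Part A and for anti-GM-CSF in Part B. As written, scheduled testing can describe Group 6 antibody about six months after the final boost, but not shortly after either boost.

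The consequence depends on a response being transient, and the documents give no probability for that. The primary and secondary endpoints are unaffected. The change is worth making because it is cheap and bears on the Part B safety evaluation of homologous boosting.

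**What to change.** In section 8.7.4.2 and the anti-IL-12 row of Appendix C, assign anti-IL-12 binding antibody to the serum already stored at Visits 9 and 11, at least for Group 6 vaccinees and placebo recipients. Leave the GM-CSF antibody tubes as they are in all groups.

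Cost: (30 + 6) participants × 2 visits = 72 additional ELISAs and a small part of the 15 mL stored at each visit, with no new visit or blood draw.

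If separate 5 mL tubes were preferred, the row would become 7 × 5 = 35 mL. The 56-day totals would rise from 430 to 435 mL at Visit 9 and from 485 to 490 mL at Visit 11, both under the 500 mL limit in section 12.3.

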#### **8.7.4.3 Cellular immunogenicity studies for Part A and Part B (Wyeth)**

Tetramer-binding assays will be performed at Wyeth on cryopreserved PBMC stored at the CSR on samples from Part A at baseline and 2 weeks post third immunization, and on samples from Part B at baseline, 2 weeks post third, fourth and fifth vaccination visits and at

the final visit. These analyses will use a panel of tetramers that represent peptides from the HIV CTL MEP in the context of the appropriate HLA molecule (See Table 2-2). The HIV CTL MEP consists of 4 CTL multiepitope peptides designated A, B, C, and J. These peptides range in length from 27 to 47 amino acids. Each hybrid peptide contains 1 of 3 different HIV T helper epitopes (and terminal amino acids sequence derived from Env or Gag) in combination with 1 of 4 different CTL “hot spots.” All Gag CTL epitopes and CD4 + T cell epitopes in HIV CTL MEP are derived from similar sequences found in GENEVAX® gag-2962. The CTL “hot spot” peptides are regions of Clade B Gag and Nef proteins that contain multiple overlapping CTL epitopes. These “hot spots” were selected for use in the HIV CTL MEP vaccine as this combination of epitopes is restricted by 19 HLA types, providing theoretical coverage for 95% African Americans, 97% Thais, 98% Caucasian Americans, and 99% Native Americans. A partial listing of the CTL epitopes and their restricting HLA alleles is provided in Table 2-2 and Table 2-3.

#### **8.7.4.4 T-cell repertoire studies for Part B (Vanderbilt University)**

HIV epitope-specific T-cell receptor (TCR) repertoires will be evaluated in vaccinees with detectable CD8+ T-cell responses. Tetramer-positive T cells from cryopreserved PBMC will be sorted and subjected to TCR analysis by PCR [100]. The breadth of TCR repertoires in vaccinees will be compared to matched, HLA-typed controls of HIV+ subjects at different stages of HIV disease. These subjects include a cohort of subjects with control of viremia (10 subjects with viral loads <50 copies off ART, and an additional 20 subjects with viral loads <1,000 copies off ART), actively followed by [name] at Vanderbilt University Medical Center. These subjects have signed an informed consent, approved by the Vanderbilt University IRB, for an observational study (NIH-funded) to identify potential correlates of control of HIV viremia.

## **8.8 HLA typing**

Molecular HLA typing may be performed on enrolled participants using cryopreserved PBMC collected at baseline, initially in participants who demonstrate vaccine-induced T-cell responses at post-vaccination time points. Other participants (including placebo recipients) may be HLA-typed to support future studies of immunological interest at the discretion of the protocol chair and the HVTN Laboratory Program. These assays may include, but are not limited to, fine epitope mapping by flow cytometry or ELISpot, or flow cytometric tetramer analysis.

## 9 Statistical considerations

### 9.1 Overview

This study is a multicenter, randomized, placebo-controlled, double-blind trial. The data analysis will evaluate safety and immunogenicity data of the study groups.

### 9.2 Objectives

The primary objective of this trial concerns safety; the secondary objectives concern immunogenicity and social impacts.

### 9.3 Endpoints

#### 9.3.1 Safety

Assessment of product safety will include clinical observation and monitoring of hematological and chemical parameters. Safety will be evaluated by monitoring participants for local and systemic adverse reactions after each injection and for 9 months after the first injection in Part A and for 15 months after the first injection in Part B. Section 14 describes the safety monitoring plan and reports.

The following parameters will be assessed:

- Local reactogenicity signs and symptoms
- Systemic reactogenicity signs and symptoms
- Laboratory measures of safety
- Adverse and serious adverse experiences

#### 9.3.2 Immunogenicity

Immunogenicity endpoints are:

- HIV-specific cellular responses assessed by IFN- $\gamma$  ELISpot assays
- HIV-specific cellular responses as assessed by intracellular cytokine staining (ICS)

#### 9.3.3 Social impacts

Social impact variables include any negative experiences or problems the participant experienced due to his/her participation in this study. The following social impacts will be followed during the course of the study: social, travel, work, school, health care, life insurance, health insurance, housing, military and any additional impacts identified by a participant.

### 9.4 Accrual and sample size

Recruitment will target 156 healthy, HIV-uninfected adult participants.

Part A will consist of 4 groups. Groups 1 and 2 will be enrolled simultaneously with participants randomized to receive either *gag* DNA or placebo (Group 1), or *gag* DNA plus *IL-12* DNA (100 mcg) or placebo (Group 2) in a (10:2) ratio within each group. Groups 3 and

4 will proceed sequentially according to dose escalation rules outlined in Sections 8.3 and 14.7.5. Groups 3 and 4 will each enroll participants randomized to receive either *gag* DNA plus *IL-12* DNA (maximum tolerated dose, MTD) or placebo in a (10:2) ratio.

Part B will consist of 3 groups (Groups 5, 6, 7) and will follow Part A according to rules outlined in Section 8.4. Groups 5, 6, and 7 will be enrolled simultaneously and randomized to receive either *gag* DNA (1500 mcg) for both prime and booster vaccinations or placebo (Group 5), or *gag* DNA plus *IL-12* DNA (MTD) for both prime and booster vaccinations or placebo (Group 6), or *gag* DNA plus *IL-12* DNA (MTD) for prime and HIV CTL MEP for booster vaccinations or placebo (Group 7), each group with a (30:6) ratio for vaccine to placebo.

Note that study design blinds participants and site staff to vaccine or placebo arms of each group, but participants will not be blinded as to which group they are in.

#### 9.4.1 Sample size calculations for safety

The goal of the safety evaluation for this study is to identify safety concerns associated with administration. Sample size calculations for safety are expressed in terms of the ability to detect rare events (e.g. serious adverse events (SAEs)).

The ability of the study to identify serious adverse experiences can be expressed by the maximum true rate of events that would be unlikely to be observed and the minimum true rate of events that would very likely be observed.

Specifically, for each vaccine arm of Part A (n=10), there is a 90% chance of observing at least 1 serious adverse experience if the true rate of such an event is at least 21%; there is a 90% chance that we would not observe at least 1 serious adverse experience if the true rate was no more than 1%.

For each vaccine arm of Part B (n=30), there is a 90% chance of observing at least 1 serious adverse experience if the true rate of such an event is at least 8%; there is a 90% chance that we would not observe at least 1 serious adverse experience if the true rate was no more than 0.35%.

Probabilities of observing 0 or 2 or more serious adverse experiences among groups of size 10 and 30 are presented in Table 9-1 for a range of possible true event rates. These calculations provide a more complete picture of the sensitivity of this study design to identify potential safety problems with the vaccine.

